## Abstract

**Background:**

Parkinson’s disease (PD) is the fastest growing neurological condition worldwide. Recent theories suggest that symptoms of PD may arise due to spread of Lewy-body pathology where the process begins in the gut and propagate transynaptically via the vagus nerve to the central nervous system. In PD, gait impairments are common motor manifestations that are progressive and can appear early in the disease course. As therapies to mitigate gait impairments are limited, novel interventions targeting these and their consequences, i.e., reducing the risk of falls, are urgently needed. Non-invasive vagus nerve stimulation (nVNS) is a neuromodulation technique targeting the vagus nerve. We recently showed in a small pilot trial that a single dose of nVNS improved (decreased) discrete gait variability characteristics in those receiving active stimulation relative to those receiving sham stimulation. Further multi-dose, multi-session studies are needed to assess the safety and tolerability of the stimulation and if improvement in gait is sustained over time.

**Design:**

This will be an investigator-initiated, single-site, proof-of-concept, double-blind sham-controlled randomised pilot trial in 40 people with PD. Participants will be randomly assigned on a 1:1 ratio to receive either active or sham transcutaneous cervical VNS. All participants will undergo comprehensive cognitive, autonomic and gait assessments during three sessions over 24 weeks, in addition to remote monitoring of ambulatory activity and falls, and exploratory analyses of cholinergic peripheral plasma markers. The primary outcome measure is the safety and tolerability of multi-dose nVNS in PD. Secondary outcomes include improvements in gait, cognition and autonomic function that will be summarised using descriptive statistics.

**Discussion:**

This study will report on the proportion of eligible and enrolled patients, rates of eligibility and reasons for ineligibility. Adverse events will be recorded informing on the safety and device tolerability in PD. This study will additionally provide us with information for sample size calculations for future studies and evidence whether improvement in gait control is enhanced when nVNS is delivered repeatedly and sustained over time.

**Trial registration:**

This trial is prospectively registered at www.isrctn.com/ISRCTN19394828. Registered August 23, 2021.

## Background

Prevention of immobility and falls in older people is a public health priority. In ageing and age-associated conditions such as Parkinson’s disease (PD), gait disorders and their consequences – most notably falls – are common manifestations. The impact of gait dysfunction and falls in PD is such that people with Parkinson’s (PwP) voted both as the top research priority in a recent James Lind Alliance and Parkinson’s UK priority setting partnership [1].

Gait impairments in PD are evident at the time of diagnosis and respond only selectively to treatment [2]. They have significant consequences, as discrete gait characteristics predict the time to first fall in a cohort of newly diagnosed PwP [3]. Progression of discrete gait impairments such as step time variability and step length variability is evident in early disease despite optimal dopaminergic treatment [4]. This reflects the contemporary view of PD as a complex multisystem disorder in which gait impairments are underpinned by deficits in multiple cortical and subcortical networks as well as age-related neurodegeneration. Novel interventions targeting dopamine-resistant gait impairments and their consequences are urgently needed.

Cognitive impairment contributes to early gait deficits [5] and conversely, gait impairments predict cognitive decline in early PD [6]. There is evidence that the loss of cholinergic neurones from the nucleus basalis of Meynert (nbM) in the basal forebrain and their projections to the frontal cortex is a major contributor to the functional decline in gait, cognition and increased risk of falls [7–10]. For example, we have recently shown that nbM volumes predict future disease-specific gait decline over three years in early PD [10]. In this study, gait pace and variability characteristics were most closely linked with nbM neurodegeneration. Furthermore, a metabolic temporal variability gait covariance network in PD was recently reported to correlate with variability of step and swing time. This network was characterised by predominantly decreased brain glucose metabolism (associated with increased step and swing time variability) in the caudate nucleus, hippocampus, and red nucleus, which all receive cholinergic input from cell groups within the basal forebrain and the pedunculopontine nucleus (PPN) [11]. Research has shown that the number of acetylcholinesterase + neurons in the PPN is reduced in PD fallers relative to those patients without balance deficits and a history of falls [12]. Cholinesterase inhibitors aimed at preventing the breakdown of acetylcholine have demonstrated some promise in the management of PD-associated gait disorder and postural instability [13]. However, drugs are not without side effects and that may be more problematic in older people with multimorbidity.

An alternative approach now being trialled is to implant stimulating electrodes into the nbM [14], although this involves major neurosurgery with equivocal outcomes. A non-invasive technique that may activate the cholinergic circuitry which has gained recent traction in a number of neurological disorders is via non-invasive vagus nerve stimulation (nVNS) [15–17]. The exact underlying mechanisms of action of this method are poorly understood, but an indirect effect impacting the cholinergic system has been postulated [18]. Neuroimaging studies have provided some evidence with increased neural activity observed in multiple regions of the forebrain containing cholinergic neurons including the caudate nucleus and thalamus [19]. Additional corroboration is provided through studies demonstrating attenuation of VNS following the application of the muscarinic agonist scopolamine in a rat model [20] and after lesioning the nbM [15]. More recently, VNS improved locomotion in a rat model of PD [21] and recent randomized controlled trials have additionally demonstrated the feasibility of VNS combined with rehabilitation therapy in improving upper limb motor function in stroke patients [22]. Based on this, adjunctive VNS may be an attractive non-pharmacological approach to improve gait and balance impairments in PD [23].

Research from our group recently assessed the effect of a single dose of nVNS on dopaminergic-resistant gait characteristics (step time variability and step length variability) [4] in a pilot study in 30 PwP [24]. Gait was measured both pre- and post-intervention during a two-minute continuous walk at a comfortable walking pace. All participants were assessed while in an ‘on’ motor state. Participants were randomised to receive either a single dose of active nVNS stimulation or sham stimulation that does not activate the vagus nerve (VN) between the pre- and post-assessments with gammaCore® handheld device, which was applied to the left side of the neck. In the active group, step time variability and step length variability decreased whereas an increase was observed in the sham group, with step length variability reaching statistical significance (-5.6 vs 25.4% change for active vs control group, *p* = 0.045). Decrements in these characteristics represent an improvement; limiting the manifold of gait variability increases gait stability [25].

This exploratory study provides data suggesting that dopamine-resistant gait characteristics improve with nVNS. It is now imperative to ascertain if the effect is enhanced when nVNS is delivered *repeatedly* and *sustained* over time. Therefore, to establish a signal of efficacy and feasibility to deliver in the home, a multi-dose study is now needed.

The aim of the Adjunctive Vagus Nerve Stimulation for Improving Neural Control of Gait in Parkinson’s Disease (AdVaNSING-PD) project is to establish the safety, feasibility, and proof of concept of a non-pharmacological, low-cost, simple-to-use, home-delivered electroceutical approach to boost cholinergic function, improve gait parameters and ultimately reduce falls risk.

## Materials and methods

### Study design

The study is a single-site, proof-of-concept, double-blind sham-controlled randomised pilot trial in patients with PD. Our trial will follow the Standard Protocol Items: Recommendations for Interventional Trials (SPIRIT) guidelines [26, 27]. The study comprises a baseline assessment visit (t_1_) followed by a 12-week treatment phase that includes remote monitoring of ambulatory activity and falls with monthly follow-up calls (t_2_ and t_3_). All participants will be invited for two follow-up visits at 12 weeks (t_4_) and 24 weeks (t_5_) with the latter to assess any long-term retention. At the end of the study, a subset of participants will be invited to contribute to a focus group discussion, to facilitate the shape of a future trial. Table 1 illustrates the SPIRIT flow diagram summarising all study procedures and outcome measures, randomisation, assessments, and interventions for each phase of the study.

**Table 1 Tab1:** SPIRIT flowchart. Abbrv. TAU, treatment as usual; MoCA, Montreal Cognitive Assessment; MDS-UPDRS-III, Movement Disorder Society-Unified Parkinson’s Disease Rating Scale Part III; H&Y, Hoehn and Yahr staging; PDQ-39, Parkinson’s Disease Questionnaire-39; GDS, Geriatric Depression Scale; CFS, Clinical Frailty Scale; GCSI, Gastroparesis Cardinal Symptom Index; LLFDI, Late-Life Function & Disability Instrument; FACIT-Fatigue, Functional Assessment of Chronic Illness Therapy-Fatigue; SRT, Simple Reaction Time; CRT, Choice Reaction Time; TMT, Trail Making Test; CANTAB, Cambridge Neuropsychological Test Automated Battery; OTS, One Touch Stockings; PAL, Paired Associative Learning

	STUDY PERIOD						
	Enrolment	Allocation	Post-allocation				Close-out
TIMEPOINT	-t_1_	0	t_1_ Start	t_2_ 4weeks	t_3_ 8 weeks	t_4_ 2 weeks	t_5_ 24 weeks
ENROLMENT							
Eligibility screen by care team	X						
Informed consent	X						
Balanced randomisation		X					
Allocation		X					
INTERVENTIONS:							
Active nVNS plus TAU		X					
Sham nVNS plus TAU		X					
ASSESSMENTS							
Questionnaires:							
MoCA			X				
MDS-UPDRS III & H&Y			X			X	X
PDQ-39			X			X	X
GDS-15			X				
CFS (v2.0)			X				
GCSI			X			X	X
LLFDI			X			X	X
FACIT-Fatigue			X			X	X
Device tolerability							X
Neuropsychological tests							
SRT			X			X	X
CRT			X			X	X
Digit vigilance			X			X	X
TMT A & B			X			X	X
CANTAB OTS			X			X	X
CANTAB PAL			X			X	X
Physical assessments							
Hemodynamic & autonomic function			X			X	X
Whole blood sample			X			X	
Grip strength			X			X	X
Gait assessment			X			X	X
Axivity monitoring			X			X	X
Falls			X	X	X	X	X
Adverse events			X	X	X	X	X
Focus group discussion							X

### Study setting

This trial is carried out at the Clinical Ageing Research Unit on the Campus for Ageing and Vitality, Newcastle University, Newcastle upon Tyne.

### Participants and eligibility criteria

We aim to recruit 40 PwP in total. This study will be used to establish proof-of-concept and feasibility allowing power calculation for a larger definitive clinical trial. Participants will be over 18 years of age but younger than 76 years of either sex and of any racial or ethnic origin. The age cut-off will be used due to the lack of safety data in older or younger participants. All participants will have a diagnosis of PD, as per the UK Brain Bank Criteria [28] and participants may be Hoehn and Yahr stages I to III [29]. All participants must be on stable medication for the preceding month and anticipated over the next three months, able to walk independently without aid for a minimum of two minutes without rest and able to provide informed consent. Our exclusion criteria include:Parkinson’s disease dementia [30] or significant cognitive impairment as determined by a score of < 21 on the Montreal Cognitive Assessment (MoCA);History of stroke, traumatic brain injury, intracranial aneurysm, intracranial haemorrhage, brain tumour or atypical parkinsonian disorder;An unstable medical condition in the last six months or planned surgeries that may involve implants within the next six months;Prescribed centrally acting anticholinergics (e.g., amitriptyline) or cholinesterase inhibitors;Severe orthopaedic or neurological (excluding PD) pathology that will adversely affect gait;Pain at the nVNS treatment site (e.g., dysesthesia, neuralgia, cervicalgia);Previous use of nVNS stimulator device, including previous participation in nVNS research;Women of childbearing potential or who are pregnant or lactating;Active participation in another interventional trial or exposure to an experimental drug or intervention;Lesion (including lymphadenopathy), previous surgery (including carotid endarterectomy or vascular neck surgery) or abnormal anatomy at the treatment site (open wound, rash, infection, swelling, cut, sore, drug patch, surgical scar[s]);Known or suspected severe atherosclerotic cardiovascular disease, severe carotid artery disease (e.g., bruits or history of TIA or stroke), congestive heart failure, known severe coronary artery disease or prior myocardial infarction;Abnormal baseline electrocardiogram (ECG) within the last year (e.g., second or third-degree heart block, prolonged QT interval, atrial fibrillation, atrial flutter, history of ventricular tachycardia or ventricular fibrillation);Uncontrolled high blood pressure (systolic > 160 mmHg, diastolic > 100 mmHg) after 3 measurements within 24 h;Previous unilateral or bilateral vagotomy;Implanted metal cervical spine hardware, other metallic implants or implantable medical devices such as deep brain stimulator, hearing aid implant, pacemaker, implanted cardioverter defibrillator, cranial aneurysm and/or cranial aneurysm clips, history of facial/orbital/metallic fragments, implanted electronic device, neurostimulator, valve replacements/stents, metallic implants/prostheses) near the stimulation site such as a bone plate or bone screw;History of syncope or seizures (within the last 2 years);Patients with active cancer or are in a recent remission of cancer;Clinically significant hypotension, bradycardia, or tachycardia;Insufficient comprehension of the English language.

The primary objectives are to develop and administer the study protocol, to establish feasibility indicators of the study and to assess compliance, safety, and tolerability of multi-dose nVNS in participants with PD. Key secondary objectives include assessing the impact of multi-dose nVNS treatment on (1) gait as proof of concept. We will be focussing on changes in dopaminergic-resistant gait characteristics including step length variability and step time variability [4] in addition to other discrete (microstructural) characteristics according to an a priori model of gait [31]; (2) changes in macrostructural gait characteristics including volume, variability pattern of walking bouts and steps as measured using seven-day free living monitoring (Axivity monitor); (3) cognition as proof of concept. Particular attention will be paid to changes in cognitive domains relating to attention and fluctuating attention and changes in executive and memory function; and, (4) falls.

### Trial design

The AdVaNSING-PD project is designed as a single-site randomised double-blind sham-controlled feasibility trial with two parallel groups and a primary endpoint of safety and tolerability after 12 weeks of self-administered nVNS with additional follow-up at 24 weeks to assess any carryover effects.

### Randomization and blinding

Patients who provide informed consent to participate and fulfil the eligibility criteria will be equally randomised using a covariate-adaptive randomisation process with a minimisation method [32] into two groups to receive either active nVNS or sham nVNS. This is achieved using the variance minimisation procedure recently proposed [33]. Allocation to groups will be stratified by age, sex, global cognition (MoCA scores) and motor severity (scored using the MDS-UPDRS-III). Both patients and researchers performing the assessments and analyses will be blinded to the intervention.

### Intervention

Patients allocated to the *active group* will receive nVNS using the gammaCore® handheld nVNS device (CE 571,753). This is a handheld device that indirectly stimulates the cervical branch of the VN within the carotid sheath. Two flat stimulation contact surfaces emit a low-voltage electrical signal burst which permeates the skin and subcutaneous structures. The electrical signal consists of a 5 kHz sinusoidal wave burst lasting 1 ms that repeats once every 39 ms (25 Hz frequency). The stimulation surface is placed on one side of the neck and the stimulus is applied for 120 s (see Fig. 1). Patients will be instructed to deliver two doses of stimulation 2–5 min apart on the left side, twice daily (in the morning and afternoon) for 12 weeks. The sham devices will be supplied by ElectroCore, LLC, manufacturers of the gammaCore® device. The sham device looks identical to the active nVNS device but does not stimulate the VN. Patients in the *sham group* will receive identical instructions to those in the active group.

**Fig. 1 Fig1:**
[figure not shown]
ElectroCore’s gammaCore nVNS device (left) and demonstrated use (right) with the device applied to the left side of the neck

Participants in both arms will be shown how to deliver the intervention at the Clinical Ageing Research Unit (Newcastle University) by an unblinded trainer after the participant’s eligibility has been confirmed and randomisation has occurred. The stimulation intensity will be controlled using the device control buttons and ramped up to a comfortable level of intensity. In addition to visual instructions, all participants receive a detailed instruction sheet on how to use the device. Participants will be phoned at weeks 4 and 8 to check progress. Following the 12-week treatment phase, participants will stop using the device, after they have additionally demonstrated their final stimulation to the assessor at the 12-week visit. This is followed by completion of the device tolerability and user questionnaire. Assessors will remain blinded.

The risk associated with the use of the gammaCore® nVNS device is minimal, and the safety profile is strong. The most common adverse events reported include local site tingling, pain, redness or itching and occur in approximately 17% of participants [34]. These adverse events are quickly resolved following discontinuation of the use of the device. Due to the theoretical risk of increased cardiac adverse events with stimulation of the right VN, participants will be asked to stimulate the left side [35]. Any adverse events (AE) will be diarised during the intervention and closely monitored until resolution, stabilisation or until it has been shown that the study procedures are not the cause. Participants who discontinue or deviate from the intervention protocol will be retained in the study as intention to treat.

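### The outcome assessor watches each participant's final stimulation at week 12, which puts the claimed assessor blinding at avoidable risk

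*Protocol article*

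**What the plan says.** Randomization and blinding makes the general claim: "Both patients and researchers performing the assessments and analyses will be blinded to the intervention".

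The Intervention section (text after Figure 1) describes who sees the device in use:

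- At the start, device use is taught "by an unblinded trainer after the participant’s eligibility has been confirmed and randomisation has occurred".
- During use: "The stimulation intensity will be controlled using the device control buttons and ramped up to a comfortable level of intensity".
- At week 12, participants stop "after they have additionally demonstrated their final stimulation to the assessor at the 12-week visit".
- Next: "This is followed by completion of the device tolerability and user questionnaire".
- Immediately after that: "Assessors will remain blinded".

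On what an observer might notice, the section says of the control device: "The sham device looks identical to the active nVNS device but does not stimulate the VN". Of the active device's known effects it says: "The most common adverse events reported include local site tingling, pain, redness or itching and occur in approximately 17% of participants".

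Table 1 schedules MDS-UPDRS III with Hoehn and Yahr staging, the Trail Making Test and adverse events at both 12 weeks (t4) and 24 weeks (t5). As the table reads, its only mark for device tolerability is at t5.

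**The concern.** The protocol separates device handling from outcome assessment at the start of treatment and then brings the two together at week 12. The person whose ignorance of the arm is meant to protect the ratings watches the intervention being delivered, and the text then restates that the blind holds.

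An assessor who forms a belief about the arm may score, time or question differently. That matters most where judgement or interaction with the participant enters the measurement. Adverse events deserve particular attention, because Trial design sets the primary endpoint as safety and tolerability after 12 weeks, which is the visit where the demonstration happens. The trial is also intended to shape a larger one, so a weak step in the procedure could be carried forward.

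**Working it through.** No arithmetic applies. The check sets the relevant statements side by side.

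**1. Is the step fixed by the document?** Yes. The article names the assessor as the person to whom the final stimulation is shown. The point therefore rests on a stated procedure, not on a detail lost when a full protocol was condensed.

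**2. Does identical appearance remove every cue?** No. It covers the look of the device only. The article does not say whether the sham can be felt or whether it can redden the skin. Three routes remain open during a demonstration: the intensity the participant chooses, the participant's reaction or remarks, and local skin effects.

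**3. Which ratings could be affected?** This depends on two facts that the article does not give: whether the demonstration comes before or after the t4 tests, and whether the same assessor rates at t5.

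| Demonstration within t4 | Assessor at t5 | Ratings exposed |
|---|---|---|
| After all t4 tests | Different | None |
| After all t4 tests | Same | t5 only |
| Before some or all t4 tests | Different | Those t4 tests |
| Before some or all t4 tests | Same | Those t4 tests and t5 |

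**4. Which outcomes depend on the rater?**

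- More exposed: MDS-UPDRS III and Hoehn and Yahr staging (rater-scored), the Trail Making Test (not described as computerised) and the eliciting of adverse events.
- Much less exposed: gait from the instrumented walkway and body-worn sensor, seven-day activity from the sensor, the computerised attention tests, and the two CANTAB tests.
- Not exposed through this step: the MoCA, which Table 1 schedules at baseline only.

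Statistical analysis compares change scores between arms for gait and cognitive outcomes. Of the more exposed outcomes, only the Trail Making Test falls among these; most of the rest of that set is instrumented or computerised.

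**5. The tolerability questionnaire.** The Intervention section places it straight after the 12-week demonstration, whereas Table 1 marks it only at t5. The article does not say who administers it. The timing conflict must be reconciled, but the t4 demonstration stands either way.

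**The case against.** The strongest reply is that seeing an identical-looking device in use is not the same as learning the arm. Sham participants receive the same instructions, intensity setting is described without distinguishing arms, and nothing in the article says what an observer would see that differs. The wording also fits a closing step carried out after the t4 tests. The main analyses are descriptive, and most compared outcomes come from instruments or a computer.

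Much of this stands, and it rules out several stronger readings:

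- A reader might infer that the blind is broken, or that the trial is not double-blind in practice. The article shows a risk, not an unblinding.
- A reader might infer that the trainer is unblinded because watching stimulation reveals the arm. No reason is given; the trainer may simply hand out the device.
- A reader might apply the cited 17% to the active arm to count participants who would reveal their allocation. The figure has no sham comparator, is not a rate per session, and is not a rate of unblinding. The article also says such effects resolve quickly once use stops.
- A reader might infer bias at both t4 and t5. Neither the order within t4 nor the t5 assessor is stated.
- A reader might infer that the assessor collects the tolerability questionnaire. The article does not say so.

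The reply does not explain why the assessor needs to be the observer at all. The article already has an unblinded staff member who handles the device, so the exposure serves no purpose that the text names.

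**Conclusion.** The point holds as an avoidable risk to assessor blinding created by a stated procedure. Exposure to the device in use extends to every participant who attends at 12 weeks, but this is not exposure to the allocation itself. Neither the chance that an assessor guesses the arm nor any resulting bias can be sized from the article.

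The conclusion rests on two assumptions: that the assessor who sees the demonstration is one of those who rate outcomes, as the text implies, and that active and sham stimulation may differ in sensation, reaction or skin effect, which the article neither states nor excludes. If the demonstration already closes the t4 visit and a different person rates at t5, the practical harm is nil and the text only needs to say so. Since the change is cheap and the outcomes at stake include adverse-event elicitation, the procedure should be changed.

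**What to change.** 1. Have the existing unblinded trainer, or other staff who do not rate outcomes, observe the final stimulation in place of the outcome assessor, and only after all t4 outcome assessments are complete.
2. Have the participant complete the tolerability and user questionnaire alone. Passing it to the unblinded trainer would be a poor exchange: tolerability is part of the primary endpoint, and a possible cue to a blinded rater would be replaced by certain unblinded collection.
3. Reconcile the timing of that questionnaire between the Intervention section (12 weeks) and Table 1 (t5).
4. Optionally, record participant and assessor guesses of the arm at the end of t4, so that the future trial has evidence on how credible the sham is.

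The cost is a change of wording and visit order, and the trainer must be available at t4 visits. No new role is needed. The change does not remove every cue: adverse events are recorded throughout follow-up and participants are asked about device problems at visits, so remarks can still reach the rater. It removes the one source that the procedure itself creates.

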### Primary outcome measures

We will primarily be examining the safety of the intervention in PwP and device tolerability by recording all adverse events reported by patients. Also, the proportion of eligible patients who agree to participate in the trial and the proportion of enrolled patients who successfully complete follow-ups will be monitored. During study visits, we will ask the participants to report any issues with using the device.

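### The text places the device tolerability questionnaire at the 12-week visit, but Table 1 schedules it only at 24 weeks, 12 weeks after the device is stopped

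*Protocol article*

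**What the plan says.** The Intervention section prescribes stimulation "twice daily (in the morning and afternoon) for 12 weeks". It then describes how treatment ends: "participants will stop using the device, after they have additionally demonstrated their final stimulation to the assessor at the 12-week visit". The next sentence reads "This is followed by completion of the device tolerability and user questionnaire", and the one after it says that assessors stay blinded.

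Table 1 (the SPIRIT flowchart under Study design) lists "Device tolerability" among the questionnaires. The row has a single X, in the last column, which is t5, 24 weeks, close-out. The t4 cell is empty. The Study design text defines t4 as the 12-week visit and t5 as the 24-week visit.

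The Trial design section states "a primary endpoint of safety and tolerability after 12 weeks of self-administered nVNS with additional follow-up at 24 weeks", the later visit being there to look for carryover. The Primary outcome measures section says the team will be "examining the safety of the intervention in PwP and device tolerability by recording all adverse events reported by patients". It adds that participants will be asked about problems with the device at study visits.

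**The concern.** The two places cannot both be followed. Study design presents Table 1 as the summary of all procedures and outcome measures, and visit checklists are usually built from such a table. A checklist built from this one would have no tolerability questionnaire at 12 weeks.

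At stake is the quality of that one instrument. At t4 the participant has just used the device. At t5 the participant has not used it for 12 weeks, and the answers depend on memory. Anyone who attends t4 but is lost before t5 gives no answers at all. A response missed at t4 cannot be recovered later in its intended form. Safety and tolerability are the trial's primary interest, so the instrument should be collected when the endpoint is defined.

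**Working it through.** The article states no figure on this point that could be reproduced. The check is to compare the passages, read the table by column position, and take one difference.

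**1. Time implied by the text.** The end-of-treatment sentences in the Intervention section run in order: final stimulation shown at the 12-week visit, device stopped, questionnaire completed, assessors remain blinded. The questionnaire sentence does not repeat the visit name, but it directly follows an event fixed at that visit. The natural reading is t4 = week 12.

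**2. Time given by Table 1.** There are seven data columns: enrolment, allocation, t1, t2, t3, t4, t5. The X for device tolerability falls in the seventh, so t5 = week 24.

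**3. Is the X displaced by text extraction?** Other rows read by the same column count serve as controls:

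| Row | Columns marked | Agrees with the text? |
|---|---|---|
| Whole blood sample | t1, t4 | Yes: blood is taken before and after the intervention |
| MDS-UPDRS III and H&Y | t1, t4, t5 | Fits the three assessment visits |
| Adverse events | t1, t2, t3, t4, t5 | Fits the visits and the calls at weeks 4 and 8 |
| Focus group | t5 | Yes: held towards the end of the trial |
| Device tolerability | t5 only | No: the text places it at t4 |

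The controls land where they should, so a shifted column is unlikely.

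**4. Gap.** The device is stopped at week 12 and the table's questionnaire falls at week 24. 24 − 12 = 12 weeks, against 0 weeks under the text.

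**5. Loss between t4 and t5.** The article gives no expected attrition, so the number of questionnaires lost cannot be calculated. As a scale only: 40 participants randomised 1:1 is about 40 / 2 = 20 per arm, so each person lost between the visits removes about 1 / 20 = 5% of an arm's questionnaires.

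**6. What is unaffected.** The primary outcome is defined through adverse events and device issues raised at visits, and that definition does not name the questionnaire. Adverse events are diarised during the intervention and scheduled from t1 to t5. None of this depends on where the device tolerability X stands.

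**7. Column label.** In the text available here the t4 heading reads 2 weeks, whereas Study design defines t4 as 12 weeks. This may be a typing or extraction slip. It does not change which column holds the X.

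**The case against.** The strongest reply is that the primary outcome does not depend on this questionnaire. It is defined by recorded adverse events and by device issues reported at visits. Adverse events are kept in diaries, followed until they resolve or stabilise, and collected at t4 whichever place is followed. The main analyses are descriptive, and the narrative gives a clear sequence that a team could follow. All of this stands, and it limits the point to the questionnaire.

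Several stronger readings are tempting, and the article does not support them:

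- A reader might infer that the whole 12-week primary endpoint would be measured 12 weeks late. It would not, because adverse events are scheduled at every time point.
- A reader might infer that the questionnaire is the only structured measure of tolerability. The article does not describe its content, and diaries and visit questions also bear on tolerability, so this cannot be shown.
- A reader might infer that site reactions, which the Intervention section puts at roughly 17%, would be undercounted. Those are adverse events, captured by diary and at visits, and a late questionnaire does not remove them. That such reactions resolve quickly after stopping also does not establish that participants forget them, so the direction of any recall error is not settled.
- A reader might fault the absence of a rule for when early stoppers complete the questionnaire. A condensed article may leave that to the full protocol, so it is no finding here.

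What the reply does not remove is the contradiction itself. One named instrument has two times 12 weeks apart, and the schedule table carries the one that does not match the endpoint.

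**Conclusion.** The point holds in limited form. The Intervention text and Table 1 contradict each other on when the tolerability questionnaire is completed. Following the table would collect it 12 weeks after the device was stopped, from recall, without anyone lost between t4 and t5. The size that can be stated is a delay of 12 weeks instead of 0; the number of missing responses cannot be derived from the article.

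This rests on two assumptions: that the questionnaire sentence refers to the 12-week visit just mentioned, and that the table's columns were extracted in their printed order, which the control rows support. It is a correction worth making before the schedule is used. It does not call the adverse-event part of the primary outcome into question.

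**What to change.** Reconcile the two places by moving the X for device tolerability in Table 1 from t5 to t4. That agrees with both the end-of-treatment sequence in the Intervention section and the 12-week endpoint in the Trial design section. In the same edit, check the t4 column heading and, if it is printed as 2 weeks, change it to 12 weeks. Any visit checklist or case report form built from the table should be checked for the same entry.

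The cost is one table cell, possibly one column label, and a check of derived forms. No procedure, visit or analysis is added.
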